## Abstract

**Background:**

In recent years, significant efforts have been directed towards the research and development of disease-modifying therapies for dementia. These drugs focus on prodromal (mild cognitive impairment, MCI) and/or early stages of Alzheimer’s disease (AD). Literature evidence indicates that a considerable proportion of individuals with MCI do not progress to dementia. Identifying individuals at higher risk of developing dementia is essential for appropriate management, including the prescription of new disease-modifying therapies expected to become available in clinical practice in the near future.

**Methods:**

The ongoing INTERCEPTOR study is a multicenter, longitudinal, interventional, non-therapeutic cohort study designed to enroll 500 individuals with MCI aged 50–85 years. The primary aim is to identify a biomarker or a set of biomarkers able to accurately predict the conversion from MCI to AD dementia within 3 years of follow-up. The biomarkers investigated in this study are neuropsychological tests (mini-mental state examination (MMSE) and delayed free recall), brain glucose metabolism ([^18^F]FDG-PET), MRI volumetry of the hippocampus, EEG brain connectivity, cerebrospinal fluid (CSF) markers (p-tau, t-tau, Aβ1-42, Aβ1-42/1–40 ratio, Aβ1-42/p-Tau ratio) and APOE genotype. The baseline visit includes a full cognitive and neuropsychological evaluation, as well as the collection of clinical and socio-demographic information. Prognostic models will be developed using Cox regression, incorporating individual characteristics and biomarkers through stepwise selection. Model performance will be evaluated in terms of discrimination and calibration and subjected to internal validation using the bootstrapping procedure. The final model will be visually represented as a nomogram.

**Discussion:**

This paper contains a detailed description of the statistical analysis plan to ensure the reproducibility and transparency of the analysis. The prognostic model developed in this study aims to identify the population with MCI at higher risk of developing AD dementia, potentially eligible for drug prescriptions. The nomogram could provide a valuable tool for clinicians for risk stratification and early treatment decisions.

**Trial registration:**

ClinicalTrials.gov NCT03834402. Registered on February 8, 2019

**Supplementary Information:**

The online version contains supplementary material available at 10.1186/s41512-024-00172-6.

## Introduction

### Background and rationale

Over the last two decades, significant efforts have been dedicated to the development of potentially disease-modifying treatments for Alzheimer’s disease (AD) [1, 2]. In recent years, phase 3 clinical trials have been completed on monoclonal antibody therapies proposed to slow down the conversion of AD, and requests for marketing authorisation have been submitted to regulatory authorities. Lecanemab was approved by the Food and Drugs Administration (FDA) in July 2023 and is currently under assessment by the European Medicines Agency (EMA). Aducanumab has received accelerated approval from the FDA for the treatment of the early stage of AD, but it has not been approved in Europe. Donanemab is headed for approval in the USA [3]. These monoclonal antibodies target amyloid plaques in the brain and are intended for those with MCI and mild AD. The MCI population has an estimated 15% incidence of dementia within 2 years, making them at higher risk for developing dementia [4]. However, this population also includes individuals who will never convert to AD, ranging from 14 to 38% depending on the study setting [4, 5]. As monoclonal antibody therapies are expensive and have non-negligible adverse effects [6], selectively targeting individuals with MCI who are at a higher risk of converting to AD dementia is needed. In this context, the Italian Ministry of Health and the Italian Medicines Agency (AIFA) initiated the INTERCEPTOR project in 2018 (https://www.interceptorproject.com) with the primary aim of evaluating the most reliable biomarker or set of biomarkers for predicting the conversion from MCI to AD dementia within a 3-year follow-up period. The study is designed as a longitudinal cohort study, where the baseline clinical and biomarker characteristics of the individuals diagnosed with MCI will be analysed in relation to their risk of conversion to AD dementia. The findings of this study will be used to identify individuals eligible for potential disease-modifying treatment in clinical practice. The secondary aim of the project is to define an optimal organisational model that can be readily implemented in clinical practice aligning with the primary goal and being economically sustainable. However, this aim is not part of the present statistical analysis plan.

### Study objectives

The primary aim of the study is to develop and internally validate a multivariable prediction model capable of identifying a biomarker or a set of biomarkers to predict the conversion from MCI to Alzheimer’s disease after 3 years of follow-up.

## Methods

The analyses outlined in this document are in full compliance with the TRIPOD statement for Transparent Reporting of the development of a multivariable prediction model for Individual Prognosis Or Diagnosis [7] (see Additional file 1). The statistical analysis plan has been finalised prior to the completion of the data collection. The study was registered at www.clinicaltrials.gov (NCT03834402) in January 2019. Details on the study protocol have been published elsewhere [8]. The analyses will be carried out using Stata v17.0 (StataCorp, College Station, Texas, USA) and R software v4.3.0 (R Foundation for Statistical Computing, Vienna, Austria).

### Study design

This is a multicentre, interventional, non-therapeutic cohort study. A sample of 500 individuals consecutively diagnosed with MCI at the Center for Cognitive Disorders and Dementia (Centri per i Disturbi Cognitivi e Demenza, CDCD) was planned to be enrolled. The follow-up process, consisting of neuropsychological and clinical assessments, is scheduled every 6 months over a 36-month observation period. Recruitment started on December 21, 2018, and the follow-up of the last recruited person will end on December 22, 2023.

### Study population

The study includes individuals of any gender, aged 50 to 85 years, with a formal diagnosis of MCI according to the National Institute on Aging-Alzheimer’s Association (NIA-AA) criteria [9]. The exclusion and inclusion criteria are provided in Table 1. Participants newly diagnosed with MCI were consecutively recruited from 19 Italian memory clinics (CDCD), which are centres with documented expertise in the diagnosis and treatment of AD and MCI, distributed across the national territory in each country’s macro-areas (Northwest, North East, Central, South, Islands) to reflect a representative reproduction of the Italian Health System organisation in this field. Each recruiting centre performed a comprehensive neuropsychological evaluation, collected blood samples for genetic testing, performed lumbar puncture for cerebrospinal fluid (CSF) analysis and acquired an electroencephalogram (EEG), FDG-PET scan and brain magnetic resonance imaging (MRI) either on site or at facilities associated with the recruiting centres. The evaluation of each biomarker and the risk group classification were carried out by four expert centres of reference selected for their expertise. Additional details regarding the organisational architecture of the project, protocol implementation and exam acquisition are reported elsewhere [8].

**Table 1 Tab1:** Inclusion and exclusion criteria

**Inclusion criteria:**
a) Age between 50 and 85 years
b) Age and education corrected mini-mental state examination score equal or superior to 24/30
c) Clinical Dementia Rating (CDR) global score of 0.5
d) Concerns about cognitive modifications, expressed as subjective complaints by the subject, or by impression by a close acquaintance or an expert clinician
e) Defective performance with reference to age and education matched controls in one cognitive domain (memory, executive function, attention, language, visuospatial function): if repeated assessments are available, evidence of performance decline
f) Preserved functional autonomy: the subject remains fully independent, even if specific performances may be slower, less efficient than usual level, with occasional errors
g) No dementia: the cognitive modifications do not significantly hamper social function or work activities
**Exclusion criteria:**
a) History of cerebrovascular disease (i.e. stroke episodes), alcohol abuse, severe medical disorders associated with cognitive impairment (organ failures, endocrine disorders, in particular thyroid disease and B12/folates deficiency); neuroimaging evidence of other potential causes of cognitive decline (e.g. subdural haematoma, malignancy); chronic treatment with psychotropic drugs; women in reproductive age
b) History of malignancy < 5 years
c) Contraindications for magnetic resonance imaging (MRI): pacemaker; spinal stimulators; defibrillator; any other condition incompatible with MRI acquisition
d) Presence of spinal malformations or any other contraindications to lumbar puncture, according to the investigator’s judgement
e) HIV infection
f) Use of drugs potentially affecting cognitive function, according to the investigator’s judgement
g) Individuals are not allowed to participate in any trial with experimental drug
**Exclusion criteria specific to lumbar puncture:**
Patients who refuse to or cannot temporarily interrupt antiplatelet or anticoagulant therapy 14 days prior to sampling visit

#### Baseline characteristics

Participants will be characterised based on all variables collected at baseline, separately for those who will convert to dementia and those who will not. These variables include socio-demographic information, medical history, physical examination, risk factors, comorbidities and concomitant medications (Additional file 2). Categorical data will be summarised by absolute frequencies and percentages. Continuous data will be summarised using mean and standard deviation for normally distributed variables and median with interquartile range for skewed distributions. Statistical comparisons will be performed using *t*-tests, Wilcoxon rank-sum tests and chi-square tests as appropriate. Statistical significance will be set at the 5% level.

### Outcomes

#### Primary outcome

The primary outcome is the conversion to AD dementia within 3 years of follow-up after the diagnosis of MCI. Visits to assess the study outcome are planned every 6 months. Follow-up time starts at the date of neuropsychological evaluation at baseline and ends at (i) date of conversion, (ii) end of follow-up, (iii) death and (iv) loss to follow-up, whichever occurs first. The conversion to dementia will be diagnosed by specialists according to the American Psychiatric Association’s Diagnostic and Statistical Manual of Mental Disorders, Fifth Edition (DSM-5) on the basis of clinical, cognitive and functional examination, including the CDR. The diagnosis will not be performed based on any of the biomarkers under study as clinicians are blinded with respect to the biomarkers evaluation which is a necessary condition to correctly evaluate the predictive performance of biomarkers and avoid biased estimation of the association between predictors and outcome. Conversion to Alzheimer’s disease is confirmed when an individual receives two consecutive diagnoses of the same type. The date of the first diagnosis will be considered as the date of conversion.

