#### Predictive performance

For each biomarker in the categorical form, the accuracy measures (sensitivity, specificity, positive predictive value, negative predictive value, overall accuracy, positive and negative likelihood ratios) will be calculated for comparison with the literature. For continuous biomarkers, the area under the receiver operating characteristic curve (AUC) will be also reported. Moreover, a univariate analysis will be conducted using the proportional hazard Cox model.

To evaluate the performance of the prediction models, several measures will be considered. The concordance c-index with its 95% CI will be provided as a discrimination measure and the extensions of binary AUC to survival analysis proposed by Harrell will be used [40, 41]. The Akaike information criterion will be provided as a measure of the goodness of fit of the model.

The added value on performance of each biomarker to the multivariable model with demographical and clinical variables will be assessed by the category-free Net Reclassification Improvement (NRI), which is the net proportion of events reclassified correctly plus the net proportion of non-events reclassified correctly. The delta AUC (difference in c-statistics) will be also provided [41], and the likelihood ratio test will be used to assess the statistical significance of the incremental contribution of each biomarker [36, 37].

In addition, to assess the predictive performance of the final multivariable model, calibration measures will also be reported [38, 42]. A calibration plot will be done by plotting the observed outcome proportion (on the *y*-axis) versus the ordered predicted outcome probabilities (on the *y*-axis) by quantile of the predicted risk. Subsequently, the calibration intercept and slope and their 95% CI will be estimated. There is a perfect calibration when the intercept is zero and the slope is one. Moreover, overall measures of performance, the Nagelkerke’s *R*^2^ and the Brier score, will be provided. The Brier score is a composite measure of discrimination and calibration with lower scores indicating improved model accuracy, and it will be calculated at a fixed time point (3 years).

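### AD conversion needs two consecutive diagnoses but visits are scheduled only to month 36, so confirmed risk labelled 3-year equals 30-month risk on the schedule as written

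*SAP article*

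**What the plan says.** All references are to the SAP article.

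- **Outcome and horizon** (Primary outcome): "The primary outcome is the conversion to AD dementia within 3 years of follow-up after the diagnosis of MCI".
- **Assessment** (Primary outcome): "Visits to assess the study outcome are planned every 6 months".
- **Confirmation** (Primary outcome): conversion to AD "is confirmed when an individual receives two consecutive diagnoses of the same type".
- **Dating** (Primary outcome): "The date of the first diagnosis will be considered as the date of conversion".
- **Schedule** (Study design): follow-up "is scheduled every 6 months over a 36-month observation period", and "the follow-up of the last recruited person will end on December 22, 2023".
- **Use of the horizon**: for the Brier score (Predictive performance), "it will be calculated at a fixed time point (3 years"). Under Model presentation and risk groups, the nomogram gives a probability of conversion at 3 years, and the risk categories are meant to inform treatment over the same horizon.

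The article does not say how to code a participant whose only AD diagnosis falls at the last visit attended. Event, censored and non-converter all remain open.

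**The concern.** The event is dated at the first diagnosis but depends on a second. If the last scheduled assessment is at month 36, a first diagnosis there has no scheduled successor. The same applies to a single AD diagnosis at the last visit before death or loss to follow-up. Confirmed events would therefore accrue only up to month 30, while results are reported for 36 months.

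What is at stake is mainly the absolute scale. The nomogram probability, the Brier score and the calibration would refer to a risk lower than the true 3-year risk. The internal calibration plot would not reveal this, because predicted and observed risks would rest on the same coded outcome. The binary accuracy tables, ROC cut-offs and risk groups also depend on who counts as a non-converter. The last of these carries an explicit requirement of at least 80% specificity for the medium–high-risk group. Without a written rule, the coding of these participants would be settled after the data are seen.

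**Working it through.** **1. Which first diagnoses can be confirmed.** Six-monthly visits over 36 months fall at months 6, 12, 18, 24, 30 and 36. A first diagnosis at month 30 can be repeated at month 36. A first diagnosis at month 36 has no later scheduled visit. The latest confirmable first diagnosis is therefore at month 30, and confirmed-event risk at 36 months equals that at 30 months.

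**2. The plan's own figures** (Sample size). 400 / (1 − 0.20) = 500. At 40% incidence, 400 × 0.40 = 160 events. The Table 2 half-width for 80% sensitivity is 1.96 × √(0.8 × 0.2 / 160) = 6.2%, as printed. The planning arithmetic reproduces; the problem lies in the outcome definition.

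**3. Events lost between months 30 and 36.** Assumptions, neither of them in the plan: constant hazard and on-time visits. With 36-month incidence I, the 30-month incidence is 1 − (1 − I)^(30/36). N = 400 is the evaluable number in the Sample size section. The 27%, 35% and 40% are the Table 2 incidences.

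| 36-month incidence | 30-month incidence | Events at 36 months | Events by 30 months | Lost | Share lost |
|---|---|---|---|---|---|
| 40% | 34.7% | 160 | 138.7 | 21.3 | 13.3% |
| 35% | 30.2% | 140 | 120.6 | 19.4 | 13.8% |
| 27% | 23.1% | 108 | 92.3 | 15.7 | 14.6% |

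With linear accrual instead, the 30-month incidence is 5/6 of the 36-month figure. The share lost is then 1/6, or 16.7%, at any incidence (40% becomes 33.3%).

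**4. Precision.** With 138.7 events, the half-width for 80% sensitivity is 1.96 × √(0.16 / 138.7) = 6.7%, against 6.2%.

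**5. Binary accuracy, if unconfirmed month-36 cases are tabulated as non-converters.** Take an illustrative marker with true sensitivity and specificity of 80%.

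- At 40% incidence, 40.0 − 34.7 = 5.3 points of converters move into the non-converter column.
  - Apparent specificity = (0.60 × 0.80 + 0.0533 × 0.20) / (0.60 + 0.0533) = 75.1%.
  - Apparent PPV = (0.3467 × 0.80) / (0.40 × 0.80 + 0.60 × 0.20) = 63.0%, against a true 0.32 / 0.44 = 72.7%.
- At 27% incidence the same formulas give specificity of 76.9%, and PPV of 51.0% against 59.7%.

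**6. Cox model, if they are censored at month 36.** These participants are correctly event-free in every risk set up to month 30. Hazard ratios and the ordering of pairs involving earlier events are then little affected. The cost is fewer events and an absolute risk that does not rise after month 30.

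**The case against.** The strongest reply is that the article leaves a gap and does not state an impossibility. It does not say that the second diagnosis must be made at a scheduled study visit, nor that unconfirmed cases are non-converters. The December 2023 date applies to the last person recruited. Recruitment began in December 2018, so early entrants reached month 36 well before the study closed, and a later confirmatory diagnosis is not excluded for them. The protocol, which is not shown, may provide one. This stands against the reading that such conversions can never be confirmed. It does not remove the point: this document defines the outcome and the visit schedule, the two do not fit at the stated horizon, and no rule bridges them.

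Other stronger readings that a reader might infer are not supported either:

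- **Biased biomarker effects.** If the cases are censored, hazard ratios and concordance against earlier events are largely unaffected. The loss of specificity in step 5 requires coding as non-converters, which the article does not prescribe.
- **Fewer candidate predictors.** Dividing 138.7 by the plan's 9.5 events per parameter gives 14.6, which suggests 14 candidates and not 17. But the planning inputs already refer to about 2.5 years: the literature incidence of 29 to 46% was seen after about that time, and the predictor calculation uses a 16% rate with average follow-up of 2.5 years (0.16 × 2.5 = 0.40). Taking months 30 to 36 off that figure is one scenario, not an established shortfall.
- **More loss after a first diagnosis.** Nothing in the article shows this, and Missing data plans telephone contact and remote visits to limit dropout. The figures above do not rely on it.

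The Discussion also reports disrupted visit timing. This moves the cut-off from person to person and makes 30 months approximate in practice, but it does not remove the gap.

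**Conclusion.** The point holds as a conflict between a stated confirmation rule and a stated schedule. Followed as written on the scheduled visits, confirmed-event risk at 36 months is the 30-month risk, while the outcome, Brier score, nomogram and risk groups carry a 3-year label. Under a constant hazard and on-time visits, about 13 to 15% of 3-year conversions would be dropped, or about 16 to 21 events in 400 at 27 to 40% incidence. Linear accrual would make it about 17%. The article says the recruitment target of 500 was missed and does not give the final number, so the counts are illustrative and the percentages carry over better.

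The harm falls on absolute 3-year risk, calibration to that risk, the Brier score and the event count. It extends to specificity and PPV only if the affected people are tabulated as non-converters. The documents do not support a claim that the hazard ratios are materially biased.

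**What to change.** Amend Primary outcome to state that, in the primary 3-year analysis, a first AD-dementia diagnosis at the last attended visit (month 36, or the last visit before death or loss) counts as a conversion at that date. Two consecutive diagnoses of the same type are then required only where a later assessment took place. Report the confirmed-only definition as a sensitivity analysis, with its horizon labelled 30 months for risk, calibration and Brier score.

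If the confirmed-only definition is to stay primary, relabel those horizons as 30 months and make the other definition the sensitivity analysis.

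The cost is a few sentences and one additional analysis. The drawback is that some single last-visit diagnoses might not have been confirmed, so the outcome is looser at the horizon being predicted. The study's own data can gauge this: report the share of earlier first AD diagnoses that were not repeated at the next visit.

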#### Secondary outcome

The secondary outcomes are the conversion to Alzheimer’s disease within 3 years of follow-up in amnesic patients and the conversion to other forms of dementia.

### Predictors

Biomarkers were selected for their accuracy in predicting the conversion from MCI to AD dementia based on the best evidence available in the literature [8]. The biomarkers under investigation include the Mini-Mental State Examination (MMSE), Delayed Free Recall (DFR) as a subscore of the Free and Cued Selective Reminding test (FCSRT), cerebrospinal fluid (CSF) parameters, (^18^F)FDG-PET, volumetric MRI, EEG for brain connectivity and APOE genotype. Details on the standardisation procedure for acquiring each biomarker are provided in Rossini et al. [8].

For CSF biomarkers, the following fluid levels are considered: threonine-181 (p-tau), total-tau (t-tau), amyloid-beta Aβ1-42, Aβ_1-42/1–40_ ratio, Aβ_1-42_/p-tau ratio. ^18^Fluorodeoxyglucose positron emission tomography (^18^F)FDG-PET is analysed with voxel-based single subject using the optimised procedure based on statistical parametrical mapping (SPM), involving a large database of normal controls for comparison and the new FDG atlas for normalisation [10, 11]. Two techniques are used to compute the right and left hippocampal volumes, normalised to the intracranial volume in volumetric MRI. The first technique is ACM-Adaboost, which is a machine learning algorithm used to classify the voxels belonging to the hippocampal region. The second technique is Freesurfer v6.0, which is a surface-based approach [12]. Seven parameters of Small World (SW) are computed in delta, theta, alpha1, alpha2, beta1, beta2 and gamma frequency bands to evaluate the brain connectivity via graph theory in EEG [13]. As part of the study, each participant is required to undergo all necessary tests for biomarker acquisition. These tests are required to be completed within 60 days from the neuropsychological battery assessment and the acquisition of informed consent at the beginning of the study. Biomarker testing is conducted in a blinded manner, meaning that the data collected at baseline, including predictor variables such as biomarkers and any information related to medical history or clinical examination, are not taken into account during biomarker testing. Moreover, to improve the predictive accuracy of biomarkers, clinical and demographic characteristics will be also considered. A critical review of the relevant literature was conducted to identify factors associated with the development of dementia [14, 15]. The following predictors, selected according to the clinical relevance among all the demographic and clinical variables collected, will be used in the development and validation of the multivariable prediction model: sex, age, level of education (measured in years of education), type of MCI (amnesic, non-amnesic) according to single or multiple domains, Amsterdam IADL (short version) [16], Cumulative Illness Rating Scale (CIRS) including severity and comorbidity index [17], hypertension, family history of dementia, smoking status, status of cohabitation as a proxy of social isolation, psychiatric disease (past and present) and cardiovascular disease. All these data, collected during the clinical assessment visit, could significantly improve the accuracy of the prediction model. All predictors are collected at baseline.
